### Statistical methods

The primary analysis population will be based on the full analysis set (FAS) and will include all randomized patients, according to the intention-to-treat (ITT) basis. All supportive analyses will be based on per-protocol set (PPS) analysis set, and the safety endpoints will be analyzed on safety analysis set (SS). The research has no plans to implement interim analysis.

All data will be entered into SPSS 10.0 software (SPSS Inc., Chicago, IL). Analyses by actual therapy include only those patients who are continuing to take their allocated therapy. Data are presented as mean and SD, range, or percentage. Data will be examined for skewness, outliers, and systematic missing data. Transformations will be undertaken as needed. Univariate and multivariate tests for repeated measures (ANOVA) are used to evaluate differences within and between groups over time. Mann–Whitney *U* test is used to evaluate differences between groups, whereas Friedman’s test (variance analysis) followed by Wilcoxon paired test is used to evaluate differences within groups. *P* < 0.05 is considered significant.

All efficacy endpoints will be analyzed in FAS, using a covariance model. Point estimates and SD for the mean change within each treatment group will be estimated. Difference within and between groups over time will be analyzed using covariance test. A last observation carried forward (LOCF) analysis will be presented for each efficacy assessment as sensitivity analysis unless otherwise specified.

The safety endpoints will be analyzed on SS. Adverse events will be summarized. The incidence of adverse events will be summarized by body system organ class and preferred term. Analyses for safety and tolerability endpoints will be summarized using descriptive statistics for continuous variables or frequency counts and percentages for categorical variables.

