### Outcomes

The primary and secondary outcomes are shown in Table 2.

**Table 2 Tab2:** Primary and secondary outcomes

	Outcome measure:
Primary outcome	
To compare the effect of exenatide versus biphasic insulin aspart 30 on glucose variability in T2DM patients inadequately controlled with metformin monotherapy.	Absolute change of MAGE from baseline to Week 16
Secondary outcome	
To compare the effect of exenatide versus biphasic insulin aspart 30 on inflammatory and oxidative stress markers, HbA1c, weight, risk of hypoglycemia and cardiovascular risk markers.	HbA1c at baseline and Week 16
	Hours of hypoglycemia assessing by CGMS at baseline and Week 16
	SMBG at baseline and Week 16
	Blood pressure and lipids at baseline and Week 16
	Body weight, BMI and WC at baseline and Week 16
	Inflammatory markers (MCP-1, hs-CRP) at baseline and Week 16
	Urinary albumin at baseline and Week 16
Safety outcome	
To evaluate the safety and tolerability of exenatide in relation to biphasic insulin aspart 30.	Adverse events/serious adverse events
	Vital signs
	Clinical hypoglycemia
	Collection of clinical chemistry/hematology parameters
	Electrocardiogram

T2DM, type 2 diabetes mellitus; MAGE, mean amplitude of glycemic excursion; CGMS, continuous glucose monitoring system; BMI, body mass index; WC, waist circumference; MCP-1, monocyte chemotactic protein-1; hs-CRP, high-sensitivity C-reactive protein

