### Sample size estimate

This study is a pilot study, which is planning to recruit 150 patients. This sample size is a justification from statistical considerations as follows:

The hypothesis on the primary endpoint is to test the mean amplitude of glycemic excursion (MAGE) in exenatide group superior to aspart 30 group. According to the literature review and previous studies, the standard deviation (SD) of change of MAGE is conservatively estimated as 3.0 mmol/L (in a pilot study of exenatide, the SD of MAGE is 2.7 to 3.1 mmol/L) [17]. With a two-sided 0.05 alpha level and a 15 % dropout rate, 150 patients with a 1:1 allocation rate (75 patients per group) will offer at least 85 % power to test a minimum 1.6 mmol/L difference on the change of MAGE between the exenatide and aspart 30 groups.

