### Assignment of interventions

Patients will be randomized 1:1 to treatment groups via a central randomization system (interactive voice/web response system (IVRS/IWRS)), and the drug will be dispensed accordingly. The study population will be stratified at randomization based on MAGE (<5.6 mmol/l and ≥ 5.6 mmol/l) and the severity of the disease (HbA1c < 9.0 % and ≥ 9.0 %).

Because the study drug (Exenatide) has an obviously different appearance from, and is used differently from, the biphasic insulin aspart 30, a definite blindness is hard and worthless for investigators and patients. Therefore, an open-label study is being conducted. Bias at randomization is reduced by the use of a central randomization system. Moreover, key efficacy parameters (MAGE, HbA1c, FPG, and postprandial plasma glucose (PPG)) will be blinded for the investigator during the course of the study (from randomization to week 16) except for the screening and pre-randomization visit. However, when FPG meets the study drug discontinuation criterion of hyperglycemia, the investigator will be alerted to conduct retest for confirmation.

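### The statistical methods give the same between-group comparison to several tests without saying which one decides the primary MAGE endpoint

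*Protocol article*

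**What the plan says.** The Outcomes table defines the primary endpoint as "Absolute change of MAGE from baseline to Week 16". The Study plan table schedules CGMS at visits 2 and 9 only, so MAGE has two time points.

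The Statistical methods section makes these statements about comparing the groups:

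- Second paragraph: "Univariate and multivariate tests for repeated measures (ANOVA) are used to evaluate differences within and between groups over time".
- Same paragraph, on the Mann–Whitney U procedure: this "test is used to evaluate differences between groups". Friedman's test followed by Wilcoxon paired tests is listed for within-group differences.
- Same paragraph, after the data are examined for skewness and outliers: "Transformations will be undertaken as needed". One 0.05 significance threshold closes the paragraph and is tied to no particular test.
- Third paragraph: all efficacy endpoints go into a covariance model on the full analysis set, and "Difference within and between groups over time will be analyzed using covariance test".

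Under Assignment of interventions, "The study population will be stratified at randomization based on MAGE" (cut at 5.6 mmol/L) and on HbA1c (cut at 9.0%). The trial is open-label, with key efficacy values withheld from the investigator until week 16.

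**The concern.** The second and third paragraphs hand one contrast, differences within and between groups over time, to two different model families. A rank test is added for the between-group part. No method is named as primary for MAGE, and nothing says when the rank test or a transformation would replace the covariance model.

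The three methods answer the question differently. With two time points, the repeated-measures group-by-time test is a t-test on change. Mann–Whitney uses neither baseline MAGE nor the randomisation strata. A covariance model can use both.

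Two things are at stake. The declared primary result can depend on which test is reported. And the two tests that do not adjust for baseline give up precision that the trial's own baseline CGMS would supply.

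**Working it through.** **Inputs from the article (Sample size estimate).** SD: "the standard deviation (SD) of change of MAGE is conservatively estimated as 3.0 mmol/L". Design: "With a two-sided 0.05 alpha level and a 15 % dropout rate", 75 patients per group, target difference 1.6 mmol/L, stated power at least 85%.

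**Assumptions not in the article.** Baseline-to-week-16 correlation ρ of MAGE of 0.3, 0.5 and 0.7; equal SD at the two visits; mean MAGE of 6 mmol/L in the simulations.

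**Step 1: reproduce the stated power.** Evaluable patients per arm = 75 × 0.85 = 63.75.

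Power ≈ Φ(δ / (σ√(2/n)) − 1.96) = Φ(1.6 / (3.0 × √(2/63.75)) − 1.96) = Φ(3.011 − 1.96) = Φ(1.051) ≈ 85.3%.

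With n = 63 the result is 84.9%, and with n = 64 it is 85.5%. The t-based values are 84.4% and 84.9%. The stated power is reproduced, for an unadjusted comparison of change.

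**Step 2: error rate with no true effect.** Simulation with 64 per arm, SD of change fixed at 3.0 and 6,000 trials per setting.

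| Rule for declaring significance | Chance of a false positive |
|---|---|
| Any single pre-named test | about 5% (4.3% to 5.3%) |
| Any of change-score test, Mann–Whitney on change, ANCOVA; normal data | 7.3% to 8.5% |
| Same three; skewed data | 8.2% to 9.1% |
| Mann–Whitney on week-16 values in place of change | 9.6% to 10.5% |
| Both rank versions plus log versions of the other two; skewed data | 12.0% to 13.0% |

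The Monte Carlo standard error at 8% is √(0.08 × 0.92 / 6000) ≈ 0.35 percentage points. For comparison, three independent tests would give 1 − 0.95³ = 14.3%. These tests are correlated, so that figure overstates the exposure.

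**Step 3: power at a true 1.6 mmol/L.** If σ is the SD of change, the SD at each visit is s = σ / √(2(1 − ρ)). The ANCOVA residual SD is s√(1 − ρ²) = σ√((1 + ρ)/2).

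| ρ | ANCOVA residual SD (mmol/L) | ANCOVA power, 63 per arm |
|---|---|---|
| 0.3 | 3.0 × √0.65 = 2.42 | 96% |
| 0.5 | 3.0 × √0.75 = 2.60 | 93% |
| 0.7 | 3.0 × √0.85 = 2.77 | 90% |

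Simulation with normal data agrees: ANCOVA about 90% to 96%, change-score test about 84% to 85%, Mann–Whitney on change about 82% to 83%. The last two hardly move with ρ because the SD of change is held at 3.0. Mann–Whitney on week-16 values ranges from 94% (ρ = 0.3) down to 62% (ρ = 0.7).

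**Step 4: disagreement.** At a true 1.6 mmol/L, at least one of the three tests is significant and at least one is not in about 16%, 13% and 11% of trials at ρ = 0.3, 0.5 and 0.7.

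**The case against.** **The covariance model may already be the primary analysis.** The third paragraph covers all efficacy endpoints on the population named as primary, and the second paragraph reads like a generic methods list. This is a fair reading and probably the intended one. But the text does not say so. The generic paragraph carries the only significance rule, is not labelled secondary or supportive, and uses almost the same phrase for the ANOVA as the third paragraph uses for the covariance test. By contrast, the LOCF analysis is expressly labelled a sensitivity analysis.

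**Covariates, transformation criteria and the trigger for rank tests usually sit in an analysis plan.** This stands. A reader might infer that the trial ignores its strata and baseline MAGE. The article does not support that: it names no covariates, and a full plan may. The finding rests on the unranked tests, not on the missing covariate list.

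**The inflation is conditional.** This also stands. A reader might infer that the 5% level is breached. Each test alone holds it, and nothing in the article says that any one significant test suffices.

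**Friedman's test and repeated-measures ANOVA are not wrong in themselves.** Fasting glucose, weight, BMI, waist circumference and lipids are measured at three or more visits, where both apply. The poor fit is limited to endpoints with two time points, such as MAGE. Friedman's test is in any case a within-group test.

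**The SD can be misapplied.** The article's supporting parenthesis cites an SD of MAGE, so a reader might use 3.0 as the SD at each visit. With ρ = 0.3 the SD of change would then be 3.0 × √(2 × 0.7) = 3.55, and change-score power would fall to about 72%. The planning value is stated for the change, so that larger loss is not supported.

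**Conclusion.** The point holds as an ambiguity in the text that bears on the primary endpoint. One contrast is given to two model families, a rank test and open-ended transformations are added, and none is named as deciding. If the choice were made after seeing the data, the false-positive chance would be about 7% to 9% for the three tests, and up to about 13% if week-16 rank tests and log versions were also allowed. At the planned effect the tests would disagree in about 11% to 16% of trials. ANCOVA would offer 90% to 96% power against about 82% to 85% for the other two.

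These sizes rest on the article's SD of change, about 64 evaluable patients per arm, the assumed correlation range and, for power and disagreement, normal data. The documents do not show that the error rate is in fact inflated, and the sample size calculation is sound.

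**What to change.** Name the covariance model as the single primary analysis: ANCOVA of change in MAGE at week 16 on treatment, continuous baseline MAGE (which carries the MAGE stratum) and HbA1c stratum (<9.0% or ≥9.0%). Fix the scale in advance, and report the adjusted difference with its 95% confidence interval. Tie the two-sided 0.05 threshold for the primary endpoint to this test alone. Label Mann–Whitney and any transformed analysis as sensitivity analyses. Restrict repeated-measures ANOVA and Friedman/Wilcoxon to endpoints measured at three or more visits.

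The cost is a few sentences in the Statistical methods section. No new data, visits or patients are needed. The article reports that recruitment is still under way, so the change can be made and dated before the data are analysed.

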Blood glucose (BG) is monitored in the study sites by a Guardian™ Real-Time CGMS (Medtronic MiniMed Inc., CA, USA), which is used to record glucose levels every 5 min for 72 h consecutively. During the second visit (baseline visit) and the last visit (end of the study), the continuous glucose sensor is inserted subcutaneously in the abdominal periumbilical area, separately. Meanwhile, a blood glucose meter is used to perform sensor calibration four times daily. The participants receive a calibration 2 hours after sensor insertion and then four glucose calibrations at each meal and before bed, and the time of each meal is marked in the consecutive 3-day test. Participants are provided the same mixed meals (30 kcal/kg ideal weight/day, based on dietitian recommendations, including 55 % of calories from carbohydrates, 25 % from fat and 20 % from proteins, with a meal distribution of 1/5, 2/5 and 2/5). They must keep a diary of meals (content and times) and avoid intensive physical activity during both CGMS periods. The dietary pattern using 3-day diet records for each CGMS study period will be checked in all participants. All the parameters of continuous glucose monitoring are calculated from each CGMS output, which is extracted using the CGMS 3.0 software package (Medtronic MiniMed, MMT-7310 version 3.0C (3.0.128), CA, USA). The mean glucose level is calculated as the mean of all the consecutive sensor readings, from which the SD is also calculated. The largest amplitude of glycemic excursion (LAGE) is defined as the maximal sensor glucose level minus the minimal sensor glucose level during each day. The MAGE is used for assessing the intraday glucose variability. MAGE is calculated by measuring the arithmetic mean of the differences in consecutive peaks and nadirs, which are taken into consideration only if they exceed one standard of deviation from the mean [18]. The mean of the daily differences (MODD), calculated as the average absolute difference of paired sensor glucose values during two successive 24-h periods, is used to assess the interday glucose variability.

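### LOCF is the named sensitivity analysis for every efficacy endpoint, but MAGE has one post-baseline measurement, so LOCF either imputes zero change or adds nothing to an observed-data analysis

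*Protocol article*

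**What the plan says.** - **Endpoint.** Table 2 (Outcomes) gives the primary outcome as "Absolute change of MAGE from baseline to Week 16".
- **Measurement times.** Data collection and management: "During the second visit (baseline visit) and the last visit (end of the study), the continuous glucose sensor is inserted". Table 3 agrees: it marks CGMS at V2 (week 0) and V9 (week 16) and at no visit between. It lists no early-termination visit.
- **Primary analysis.** The full analysis set "will include all randomized patients, according to the intention-to-treat (ITT) basis". On the model, Statistical methods says: "All efficacy endpoints will be analyzed in FAS, using a covariance model".
- **Missing data.** The same section says: "A last observation carried forward (LOCF) analysis will be presented for each efficacy assessment as sensitivity analysis unless otherwise specified". Nothing different is then specified for MAGE. The only other mention is "Data will be examined for skewness, outliers, and systematic missing data", which describes inspection and not handling.
- **Expected loss.** Sample size estimate: "With a two-sided 0.05 alpha level and a 15 % dropout rate".

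**The concern.** LOCF needs an intermediate value to carry. MAGE has none, because each patient has one baseline and at most one post-baseline recording. The rule the article fixes for every efficacy endpoint therefore does not fit the schedule of the primary one.

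Two readings are possible for a patient without a week-16 recording:

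1. **Baseline may be carried.** The imputed change is exactly 0 and is treated as if it had been measured.
2. **Only post-baseline values may be carried.** The patient has nothing to carry and is left out, so the LOCF analysis is the same as one of observed data.

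At stake is what the sensitivity analysis can tell a reader. The trial is open label, and the Assignment of interventions section refers to a hyperglycaemia criterion for stopping study drug, so loss of data could be related to arm and to glycaemic response. A sensitivity analysis should show how far the result depends on assumptions about the missing values. Reading 2 makes no such check, and reading 1 makes it at a single point.

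**Working it through.** **Inputs from the article (Sample size estimate):** difference 1.6 mmol/L, SD of change 3.0 mmol/L, two-sided alpha 0.05, 75 per arm, 15% dropout.

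**Assumptions (not in the article):** the mean change in each arm, any inequality of dropout between arms, and dropouts having the same true mean change as completers in their arm. Comparisons are unadjusted. Negative changes are reductions; differences are given as the size of the advantage for exenatide.

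**Step 1: the plan's own figure.** Evaluable per arm = 75 × 0.85 = 63.75. SE = 3.0 × √(2/63.75) = 0.531. Power = Φ(1.6/0.531 − 1.96) = 85.3% (84.8% with the noncentral t). The stated 85% reproduces and is not in dispute.

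**Step 2: patients affected.** 0.15 × 150 = 22.5, so about 22 patients without a week-16 MAGE.

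**Step 3: LOCF under reading 1.** With dropout d and true change m, the arm mean becomes (1 − d)m. The difference in size is (1 − d_I)m_I − (1 − d_E)m_E. Assumed changes are m_E = −3.0 and m_I = −1.4, which differ by the article's 1.6.

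| Dropout, exenatide / insulin | Calculation | LOCF difference (mmol/L) |
|---|---|---|
| 15% / 15% | 0.85 × 3.0 − 0.85 × 1.4 | 1.36 |
| 20% / 10% | 0.80 × 3.0 − 0.90 × 1.4 | 1.14 |
| 10% / 20% | 0.90 × 3.0 − 0.80 × 1.4 | 1.58 |
| 25% / 5% | 0.75 × 3.0 − 0.95 × 1.4 | 0.92 |
| 5% / 25% | 0.95 × 3.0 − 0.75 × 1.4 | 1.80 |

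The first row does not depend on the assumed arm changes: 0.85 × 1.6 = 1.36. Varying the insulin change from 0 to −2, with the 1.6 difference kept, gives 1.28 to 1.08 at 20%/10% and 1.44 to 1.64 at 10%/20%.

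**Step 4: precision and power of the LOCF estimate.** Arm variance = (1 − d) × 3.0² + d(1 − d)m². At 15% in both arms with m = −3.0 and −1.4:

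- Exenatide: 7.65 + 0.1275 × 9.00 = 8.80.
- Insulin: 7.65 + 0.1275 × 1.96 = 7.90.
- SE = √((8.80 + 7.90)/75) = 0.47, about 11% below the 0.53 that the observed patients support, because the imputed zeros count as measurements.
- For an insulin change of 0 to −2, power of the LOCF comparison is 84.6% to 80.5%.

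**Step 5: no true difference.** With both arms changing by −2.0 and 20%/10% dropout, the arm means are −1.6 (exenatide) and −1.8 (insulin), a false 0.2 mmol/L in favour of insulin. For common changes of −1 to −3, the false difference is 0.1 to 0.3 and the two-sided rejection rate 5.6% to 9.5% instead of 5%. Reversing the dropout rates reverses the sign.

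**Step 6: LOCF under reading 2.** No imputation takes place, so there is nothing to compute.

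**The case against.** The strongest reply is that LOCF is only a sensitivity analysis. The primary result comes from the covariance model in the full analysis set, and no figure in the working is a bias in that result. This stands.

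Four stronger readings are tempting, and the article does not support them:

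- **That the primary analysis is really a completers analysis.** The article does not say what the covariance model does with a missing week-16 value. That may be settled in the SAP or full protocol and is not part of this point.
- **That LOCF cannot test robustness at all.** Under reading 1, zero change is a definite alternative assumption. With equal dropout it shrinks a true difference, so a superiority result that survives it says something. What holds is that it is a single crude assumption that is never varied.
- **That LOCF always works against exenatide, and heavily.** The drop to 0.92 needs assumed arm changes and 25% versus 5% dropout. The reverse gives 1.80, above the true 1.6. At the only rate the article states, taken as equal, the power loss is about 1 to 5 points.
- **That every dropout receives a zero.** This requires baseline to be eligible for carrying and no closing sensor recording at withdrawal. A condensed article may leave withdrawal procedures to the full protocol.

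The qualifier allowing for other specifications leaves room for a different method, but the article gives none for MAGE. The mismatch is therefore in a rule that is stated and not in detail that was left out.

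**Conclusion.** The point holds in a limited form. As the article is written, LOCF for MAGE is either a zero-change imputation or a repeat of an observed-data analysis, so the sensitivity analysis named for the primary endpoint checks one fixed assumption or none.

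Its size under reading 1 is a reduction from 1.6 to 1.36 mmol/L at 15% dropout in both arms. With unequal dropout the estimate moves in a direction set by which arm loses more patients, and a false difference of 0.1 to 0.3 mmol/L is possible where none exists. The 1.36 rests on the article's own figures plus equal dropout and dropouts resembling completers; the rest also depends on assumed arm changes or unequal loss.

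The same mismatch applies to MCP-1, hs-CRP, 8-iso-PGF2α and urinary albumin, which Table 3 marks only at V2 and V9. HbA1c is less certain: Table 3 marks it at V1 and V9, while the meal-test text in Data collection and management lists visits 1, 2 and 6. Fasting glucose and weight have intermediate visits, so LOCF has values to carry there.

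**What to change.** In Statistical methods, limit the LOCF sentence to endpoints with intermediate visits, such as fasting glucose and weight. For MAGE and other endpoints with a single post-baseline value, state instead:

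- **Multiple imputation** of the missing week-16 value, separately by arm, from baseline MAGE, HbA1c, and the fasting glucose, weight and SMBG already collected at intermediate visits (Table 3 has all three at weeks 4, 8 and 12). Analyse the imputed data in the same covariance model and combine the results in the usual way.
- **A delta-adjusted (tipping-point) version**, in which the imputed values are shifted by increasing amounts, separately by arm, over a range fixed in advance, and the shift at which the conclusion changes is reported. This varies the assumption, which LOCF does not.

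With about 11 missing values per arm at the planned rate (0.15 × 75 = 11.25), the imputation model should be kept small.

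The cost is a change of wording and modest extra programming, in software that supports multiple imputation; the package named in the article should be checked for this. No new visit or measurement is needed. Seeking the week-16 recording from patients who stop study drug would reduce the problem at source, but the article neither confirms nor excludes that this is already done. If it is not, it would be a procedural change and is not part of this fix.
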